### 4.3.2 Data collection and investigators

The data collection will be carried out by trained and blinded raters (doctors, physiotherapists) at baseline, post-intervention and at the follow-up call. After the end of the intervention, the participants' experience and acceptance of the intervention will be assessed in focus groups. A follow-up call will take place one month after the end of the intervention, i.e. two months after the baseline assessment. This survey will include a very short interview, the fall rate during the 4-week intervention period and two questionnaires (FOGQ, FES-I).

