| Depression                                                                                                                               | Beck Depression Inventory-II (BDI-II)                                                                                     |  | X |   | X |   |
| Fall rate                                                                                                                                | Number of falls (a) in the 3-month period before study entry (BL), (b) intervention period (PI) and (c) 4-week follow-up. |  | X |   | X | X |
| Feasibility of a larger randomised controlled trial                                                                                      |                                                                                                                           |  |   |   |   |   |
|                                                                                                                                          | Recruitment rate                                                                                                          |  | X |   |   |   |
|                                                                                                                                          | Retention rate                                                                                                            |  |   |   | X | X |
|                                                                                                                                          | Adherence rate                                                                                                            |  |   | X |   |   |
|                                                                                                                                          | Adverse events                                                                                                            |  |   | X | X |   |
|                                                                                                                                          | Acceptance of the intervention (continuous: narrative; focus groups in intervention group 1)                              |  |   | X | X |   |

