#### **4.4.13 Fall rate**

There is a survey of the number of falls

- (a) in the 3-month period before the start of the study (subjectively asked at baseline)
- (b) in the 4-week intervention period (observed and subjectively asked about post-intervention)
- (c) in the 4-week follow-up period (subjectively asked during the follow-up call)

The number of falls is documented in the CRF.

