## 5.6 Data analysis

### 5.6.1 Statistical data analysis

Statistical data analysis is performed using IBM SPSS software, version 26.0 (IBM Corporation, Armonk, NY, USA) and Tobii Pro Lab Analyser (Tobii, Danderyd, Sweden). The statistical significance level is defined by a p-value of  $<0.05$ . An attempt is made to avoid missing data by inspecting the questionnaires after completion and, in case of unanswered items, asking the study participants to complete them. The number of missing data is noted; due to the less sensitive topic of the study, it is assumed that missing variable values can be assigned to "missing completely at random" or "missing at random". An intention-to-treat analysis is performed for all cases analysed in their originally assigned group.

Descriptive statistics are used for demographic data and primary and secondary outcomes. Counted and nominal scaled data (gender, fall rate, recruitment, retention and adherence rate, number of missing data if applicable, number of adverse events) are reported as whole numbers or percentages. Ordinal scaled variables (MMSE, UPDRS, H & Y, FGA, BBS, PDQ-39, FOGQ, FES-I, BDI-II) are expressed as median (minimum, maximum or interquartile range) and metric variables (TUG, TUGman, FSST, 10MWT, eye movements: Saccade velocity, amplitude, latency, fixation duration) by mean (95% confidence interval, CI or standard deviation, SD). The data is also presented graphically (e.g. by bar charts, box plot or line graphs).

The eligibility rate (%) is the percentage of patients suitable for the study after applying the inclusion and exclusion criteria from the Parkinson's patients treated at the Reha Zentrum Münster during the study period.

The recruitment rate (%) is determined as follows:  $(N_{\text{Consent}}/N_{\text{eligible}}) \times 100$ ; where  $N_{\text{Consent}}$  is the number of participants who signed the informed consent form;  $N_{\text{eligible}}$  is the number of patients eligible for the study based on the inclusion and exclusion criteria.

The retention rate (%) is calculated as follows:  $(N_{\text{completed}}/N_{\text{Total}}) \times 100$ ; where  $N_{\text{completed}}$  is the number of participants who completed the study;  $N_{\text{Total}}$  is the total number of participants in the study.

Adherence rate (%) is determined as follows: (Actual number of exercise sessions/planned number of training sessions)\*100 (Osterberg & Blaschke, 2005).

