Differences between the two groups and test times are calculated for ordinal data as follows: New variables are generated from the difference between the post-intervention and baseline data. The difference between group 1 and 2 is determined using the Mann Whitney-U test. For the ordinal variables FES-I and FOGQ, which are also collected at the follow-up call, a Kruskal Wallis test is performed across all groups and test time points. Changes in fall rate (nominal) between baseline, post-intervention and follow-up will be calculated using Chi-Square test. Metric data will be tested for homogeneity of variance (Levene test) as the basic assumption of a 2 x 2 ANOVA, with "time (baseline, post-intervention)" as the within-factor and "group (1, 2)" as the between-factor. If there is no homogeneity of variance, an alternative F-statistic (e.g. according to Welch or Brown-Forsythe) is used. If the basic assumption of sphericity is not met, corrected values are used, e.g. according to Greenhouse-Geisser or Huynh-Feldt. To calculate the differences between the groups and measurement times, a 2 x 2 ANOVA (analysis of variance) is performed, followed by pairwise comparisons (Bonferroni correction for all comparisons) between the groups at measurement times 1 and 2 if statistical significance is present. In the case of failure of the adaptive measures, non-parametric tests are used as described for ordinal scaled data.

The effect size is given by partial Eta squared and standardised effect size (Cohen's d).

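### Fall rate is tested by Chi-square across a 3-month and two 4-week windows with no scaling for time, and no post-baseline comparison of the arms is stated

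*Protocol*

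**What the plan says.** Table 2 in section 4.3.3 defines the endpoint as "Number of falls (a) in the 3-month period before study entry (BL), (b) intervention period (PI) and (c) 4-week follow-up". Section 4.4.13 gives the same three windows with their sources: "in the 3-month period before the start of the study (subjectively asked at baseline"), "in the 4-week intervention period (observed and subjectively asked about post-intervention") and "in the 4-week follow-up period (subjectively asked during the follow-up call"). It adds: "The number of falls is documented in the CRF". Synopsis endpoint 2.10 agrees.

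Section 5.6.1 places fall rate among the counted and nominal variables, which "are reported as whole numbers or percentages". Its only inferential rule for falls is: "Changes in fall rate (nominal) between baseline, post-intervention and follow-up will be calculated using Chi-Square test". The synopsis repeats that sentence. The other post-baseline rules are a Mann-Whitney test on change for ordinal data and a 2 x 2 ANOVA for metric data. Fall rate is in neither list.

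Sections 2.4 and 2.5 state the secondary hypotheses, fall rate included, as a difference or no difference between the two programmes.

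Section 4.3.2 describes the follow-up call as covering a short interview, "the fall rate during the 4-week intervention period and two questionnaires (FOGQ, FES-I").

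**The concern.** A count of falls depends on how long one counts. About 13 weeks are set against 4 and 4, so the baseline column will be larger even if nothing happens to the patients. A test of equality across the three periods then picks up window length and presents it as a change in falls.

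The rule also tests a different question from the hypothesis. It names time points and no group factor, so even a correct test of time would not estimate the effect of adding gaze training. Section 5.6.1 says the preliminary inferential analysis is meant to inform the sample size of a larger trial from differences between groups. For falls, no such difference is planned.

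A Pearson Chi-square further treats the three periods as independent samples, although the same patients supply all of them.

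Finally, section 4.3.2 and section 4.4.13 disagree about which period the follow-up call asks about. A form built from section 4.3.2 alone would collect the wrong window.

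**Working it through.** **Inputs from the protocol.** Windows of 3 months, 4 weeks and 4 weeks (section 4.4.13, Table 2); significance at p < 0.05 (section 5.6.1); 34 participants, 17 per arm (section 4.1.2.3). The protocol computes no figure for falls. Its sample size reproduces: 30 / (1 − 10/100) = 33.3, rounded up to 34.

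**Assumption.** No fall rate is given, so I used 0.1 to 1.0 falls per person per 4 weeks. The rate was either shared by all patients (Poisson) or varied strongly between them (gamma-Poisson, shape 0.5). Each patient's rate was held constant over all three windows.

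**Step 1: window ratio.** 91.3 days / 28 days = 3.26; 13 / 4 weeks = 3.25; counting 3 months as 12 weeks, 12 / 4 = 3.0. The apparent drop in raw falls at a constant rate is 1 − 1/ratio: 1 − 4/13 = 69%, or 1 − 4/12 = 67%. This needs no assumed fall rate.

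**Step 2: expected values for n = 34.** Falls per window = 34 × rate × window length in 4-week units. Under a shared rate, the faller proportion = 1 − exp(−rate × window length).

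| Falls per 4 weeks | Falls, 3 months | Falls, each 4 weeks | Fallers, 3 months | Fallers, each 4 weeks |
|---|---|---|---|---|
| 0.1 | 11.1 | 3.4 | 28% | 10% |
| 0.25 | 27.7 | 8.5 | 56% | 22% |
| 0.5 | 55.4 | 17.0 | 80% | 39% |
| 1.0 | 110.9 | 34.0 | 96% | 63% |

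**Step 3: how often the planned test rejects with no true change.** Pearson Chi-square, 2 df, nominal 5%, n = 34, 5000 simulated trials per setting. The test was applied to fallers yes/no by period, and to total falls by period against equal expectation.

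| Falls per 4 weeks | Fallers, shared rate | Fallers, varying rates | Totals, shared rate | Totals, varying rates |
|---|---|---|---|---|
| 0.1 | 57% | 32% | 62% | 57% |
| 0.25 | 87% | 46% | 94% | 93% |
| 0.5 | 97% | 45% | about 100% | about 100% |
| 1.0 | 97% | 34% | 100% | 100% |

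Entries move by a few points between repeat runs. Total falls at the lowest rate settle near 60% under either distribution, and the faller version spans about 32–98%. Counting 3 months as 12 weeks lowers the percentages somewhat without changing the picture.

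**Step 4: isolating the cause.** With three equal windows and all else unchanged, the test on totals rejects in about 5% of trials. The faller test rejects in about 5% with a shared rate and 0.3–2.7% with varying rates. The excess therefore comes from window length. Ignoring the pairing makes the faller test conservative and does not add to the artefact.

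**Step 5: which period the call covers.** Synopsis endpoint 2.10, Table 2 and section 4.4.13 all require falls in the 4-week follow-up period. Section 4.3.2 alone names the intervention period.

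**The case against.** The strongest reply is about weight. Fall rate is the tenth of the clinical secondary endpoints in the synopsis, in a 34-patient pilot whose inferential analysis is called preliminary. Falls are not a feasibility criterion in section 4.4.14. The test decides neither the primary conclusion nor whether a larger trial goes ahead. That stands, and it sets the severity.

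Four stronger readings are tempting and are not supported:

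- A reader might infer that the test would nearly always show a significant drop. That fits total falls at moderate or high rates. On fallers yes/no, the natural reading of nominal, most simulated trials with strongly varying rates do not reject (32–46% do).
- A reader might infer that the arms are never compared. The text supports only that no post-baseline between-arm test of falls is stated. Because the hypotheses are between-arm, a Chi-square by group may have been intended. Both arms share the same windows, so that test would be free of the artefact: with no effect, a between-arm comparison of fallers at post-intervention rejects in about 3–6% of trials. But the sentence in section 5.6.1 names time points only. Running the time test within each arm does not help: at n = 17 it still rejects in 12–76% of trials on fallers and 33–100% on counts.
- A reader might infer that follow-up falls would go uncollected. Three other places require them, so section 4.3.2 is an inconsistency to correct.
- A reader might give falls more weight because of the title. It names fall risk, which the protocol also attaches to cut-offs on the FGA, TUG, TUGman and BBS.

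The term fall rate could hint at scaling to time. The protocol nevertheless defines it as a number of falls and gives no denominator.

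**Conclusion.** The point holds as a should-fix. The protocol fixes the scale, the contrast and the test for falls. The contrast mixes a window of about 13 weeks with two of 4 weeks, without adjustment. The 67–69% apparent drop in raw falls at a constant rate is arithmetic from the stated windows. The false-positive rates (about 32–98% on fallers yes/no, 60–100% on total falls, at nominal 5%) rest on assumed rates of 0.1–1.0 falls per 4 weeks and on the two distributions tried. The drop in the faller percentage is smaller than 69% at high rates, for example 96% to 63% at 1.0 per 4 weeks. Separately, the stated rule gives no estimate of the between-arm effect that sections 2.4 and 2.5 ask for. The pairing problem is a genuine flaw in the test, but it works in the conservative direction. A separate analysis plan would need to override the protocol's sentence, because the protocol does not leave the choice open.

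**What to change.** In section 5.6.1 and the synopsis, replace the Chi-square sentence with the following:

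- Report falls per person-week by arm and period.
- Report a between-arm rate ratio with 95% CI for falls after baseline. Use one total per patient over the post-baseline weeks observed, or analyse each period separately, so that no patient enters one model twice.
- Use a Poisson model with robust standard errors, log(weeks observed) as offset and arm as the effect. Add baseline falls per week and the H&Y stratum only if there are enough events.
- If an arm has very few or no falls, use an exact rate ratio and note that it ignores overdispersion.

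A richer count model over both periods would be fragile: at 0.1–0.25 falls per 4 weeks, only 3.4–8.5 falls are expected per 4-week period in all 34 patients. It would also need to handle the correlation between a patient's two periods.

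Reconcile section 4.3.2 with synopsis 2.10, Table 2 and section 4.4.13 on the period the follow-up call covers, and check the CRF against the result.

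The cost is a few sentences in two places, one correction in section 4.3.2 and one simple model, with no new data beyond what section 4.4.13 already requires. The downside is that the rate ratio will be imprecise at n = 34.

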## 2.4 Null hypotheses

**Primary null hypothesis:** There is no difference between the effects of an everyday physiotherapy training programme with eye movement training and such a training programme without eye movement training on dynamic balance in people with idiopathic Parkinson's syndrome.

**Secondary null hypotheses:** There is no difference between the effects of an everyday physiotherapy training programme with gaze movement training and such a training programme without gaze movement training on functional mobility with and without manual multi-task, static balance, walking speed, health-related quality of life, freezing of gait, fall-associated self-efficacy, depression, fall rate and eye movements during dynamic balance tasks and specific training items in individuals with Idiopathic Parkinson's Syndrome.

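### Fall counts from a 3-month and two 4-week windows are tested by chi-square across time, with no exposure time and no stated comparison of the arms

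*Protocol*

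**What the plan says.** Table 2 (Protocol 4.3.3) defines the fall endpoint as "Number of falls (a) in the 3-month period before study entry (BL), (b) intervention period (PI) and (c) 4-week follow-up". Section 4.4.13 gives the same three windows: the first "in the 3-month period before the start of the study (subjectively asked at baseline)", the second "b) in the 4-week intervention period (observed and subjectively asked about post-intervention)", the third "c) in the 4-week follow-up period (subjectively asked during the follow-up call)". It adds: "The number of falls is documented in the CRF". Section 5.6.1 groups fall rate with counted and nominal data, to be shown as whole numbers or percentages.

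The one inferential sentence on falls, in 5.6.1 and again in the synopsis, is "Changes in fall rate (nominal) between baseline, post-intervention and follow-up will be calculated using Chi-Square test".

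The secondary null hypothesis (2.4) states no difference between the programmes with and without gaze training on a list that includes "depression, fall rate and eye movements during dynamic balance tasks". The alternative in 2.5 mirrors it.

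**The concern.** The word rate is only a label here: nothing in the protocol puts the three counts on a common time base. A test of change across windows of unequal length responds to the length of the window as well as to the patients' falls. Because the long window comes first, the error runs in the favourable direction.

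Two further problems come with the choice of test. A Pearson chi-square assumes independent observations, but the same patients appear in all three windows and one patient may fall repeatedly. The sentence also compares time points, while the hypothesis compares programmes.

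Fall risk is in the trial's title and fall rate is in the research question (2.2). Followed literally, the analysis can show an apparent fall reduction when nothing changed, and it does not say whether gaze training affected falls. None of this depends on how well falls are captured.

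**Working it through.** **Inputs from the protocol.** Windows: 3 months, 4 weeks, 4 weeks (Table 2, 4.4.13). Significance level 0.05 (5.6.1). Sample size 34, 17 per arm (4.1.2.3). The plan's own size figure reproduces: 30 / (1 − 0.10) = 33.3, rounded up to 34. No expected fall rate and no power for falls are given.

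**Assumptions.** True fall rate constant over time and equal in both arms, at 0.02 to 0.5 falls per patient per 4 weeks. Falls are Poisson, or Poisson with gamma-distributed differences between patients (variance up to 2).

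**Step 1, window length.** Taking 3 months as 12 weeks, the ratio is 12/4 = 3.0; as 13 weeks, 13/4 = 3.25; as 91.3 days, 91.3/28 = 3.26. With an unchanged rate the number of falls drops by 1 − 1/3.0 = 67% to 1 − 1/3.26 = 69%.

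**Step 2, worked cases with an identical rate throughout.** Chi-square = Σ(O − E)²/E on 2 degrees of freedom.

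- 12, 4, 4 falls, equal expectation 20/3 = 6.67: (5.33² + 2.67² + 2.67²)/6.67 = 6.4, p = 0.041. Against a 3:1:1 expectation (12, 4, 4), chi-square = 0, p = 1.00.
- 55, 17, 17 falls (0.5 × 34 = 17 per 4 weeks; 17 × 3.25 ≈ 55), equal expectation 89/3 = 29.67: (25.33² + 12.67² + 12.67²)/29.67 = 32.4, p = 9 × 10⁻⁸. Against 13:4:4, chi-square = 0.0004, p = 1.00.
- With few falls the test does not reach significance: 9, 3, 3 gives p = 0.091 and 6, 2, 2 gives p = 0.20.

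**Step 3, how often a false change appears.** Simulated trials of 34 patients with a baseline window of about 13 weeks and no true change. Counts are tested against equal expectation; fallers are tested in a 3 × 2 table of window by fell or did not fall. The lower faller figures come from strong differences between patients.

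| Falls per patient per 4 weeks | Counts | Fallers |
|---|---|---|
| 0.02 | about 13% | about 10–12% |
| 0.05 | about 34% | about 21–29% |
| 0.1 | about 60% | about 34–56% |
| 0.3 | about 96–98% | about 46–91% |
| 0.5 | over 99% | about 45–97% |

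At rates of 0.1 and above, practically all the false changes on counts are towards fewer falls. With 30 evaluable patients the count figures are a little lower (about 55–56% at 0.1 and 94–96% at 0.3); taking 3 months as 12 weeks also lowers them somewhat.

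**Step 4, what removes it.** At rates of 0.1 to 1.0, weighting the expected counts by window length brings the false-positive rate to 4.1–5.0%. A group-by-window table of counts gives 3.4–5.3%, because both arms share the same windows and their length cancels.

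**Step 5, the contrast.** The neighbouring sentences of 5.6.1 name groups: Mann-Whitney between groups 1 and 2, Kruskal-Wallis over groups and time points for FES-I and FOGQ, ANOVA with group as the between-factor. The fall sentence names only baseline, post-intervention and follow-up. The Fisher test for nominal data is a baseline comparison, and the synopsis list for it omits fall rate.

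**The case against.** **A reader might infer that an unchanged rate is bound to be declared a fall reduction.** The documents do not support that. No fall rate is given, and at low rates most trials would show nothing: about two thirds at 0.05 and nearly nine in ten at 0.02. The test is also non-directional, so calling the result a reduction is a step taken in reporting. What stands is an inflated risk of a false change, not a certainty.

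**The label nominal suggests fallers rather than counts.** That is a fair reading, and it gives smaller figures. If the test were run within each arm (17 patients) with strong heterogeneity, the false-change rate would be about 14–19%. Every reading examined still exceeds 5%.

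**A reader might also infer that the arms are never compared on falls.** That is stronger than the text. The table layout is not given, analysis is by assigned group, and nominal data have a baseline test between groups. A group-by-window table may have been intended and would remove the inflation. The supportable statement is that no between-arm test of on-study falls is stated; if one was meant, the sentence still has to say so.

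**This is a pilot.** Falls are one of many secondary endpoints, inference is preliminary, falls have no target rate among the feasibility criteria in 4.4.14.1, and the later sample size rests on mean differences. This lowers the priority but does not make the test right.

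**A count model may be too much for 17 per arm.** At 0.1 falls per 4 weeks, 17 × 0.1 = 1.7 falls are expected per arm per window. This stands, so the fix needs a rule for sparse data.

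**Conclusion.** The test is wrong as written and should be fixed before analysis; the primary endpoint is untouched. The windows, the scale and the test are all fixed in the protocol, and together they give a test of the wrong contrast with a false-positive rate above its nominal 5%. That conclusion does not depend on the assumed fall rate, but its size does: from about 13% at 0.02 falls per patient per 4 weeks to at least 96% from 0.3 on counts, and about 10% to 97% on fallers depending on rate and heterogeneity. These figures assume 34 patients, a baseline window of about 13 weeks, a constant true rate and a table by time point only.

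**What to change.** In 5.6.1 and the synopsis, replace the fall sentence as follows.

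- Express falls per patient-week in each window and show change over time descriptively only.
- Compare the arms on on-study falls. Fix in advance whether the two 4-week periods are pooled or analysed separately. Use a count model with log(weeks observed) as offset, arm as factor and, where it can be fitted, baseline falls per week as covariate. Report the rate ratio with 95% CI.
- Pre-specify a numeric minimum number of falls. Below it, compare the proportion of fallers per 4-week window between arms by Fisher's exact test, or report it descriptively by arm; state which.
- Reconcile 4.3.2, where the follow-up call asks about falls in the intervention period, with Table 2 and 4.4.13, where it covers the 4-week follow-up. Until that is settled, the data for the follow-up comparison are not assured.

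The cost is wording in two places plus this reconciliation. If the call does cover the follow-up period, no new data are needed. With 17 per arm the rate ratio will be imprecise, and the report should say so.
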